**Figure 1 F1:**
[figure not shown]
Patient flows showing randomisation, intervention period and follow-up period. CPB, cardiopulmonary bypass.

#### Trial-specific tests and procedures

Participants will undergo research tests and procedures. These are in addition to tests and procedures undertaken as part of standard of care (SOC). However, if the routine samples are not taken as part of SOC, then these blood samples will be taken for the trial as additional volumes.

A full blood count will be carried out by the hospital laboratory. Serum creatinine and liver function tests will be analysed in the hospital laboratory. Microvesicles, platelets, leucocytes and endothelial cell activation will be analysed by microfluidics and flow cytometry. In addition to these tests, the results of routinely collected arterial blood lactate values will be used to assess the time to clearance of the oxygen debt. These tests are measured in an ad hoc manner as dictated by a range of clinical requirements but as a rule of thumb are measured hourly for the first 4 hours post admission to ICU then every 2–4 hours thereafter until discharge. The frequency of these tests will not be influenced by recruitment in the trial.

Collection of tracheal aspirate, aspirate of tracheal secretions, may be used to measure pulmonary leucocyte extravasation and protein concentrations. At 4–6 hours postsurgery, bronchial suction will be performed as SOC for ventilated patients. If necessary, we will administer 5 mL of normalised saline via the endotracheal tube and aspirate bronchial secretions using an aseptic technique. This aspirate will be analysed for protein concentrations and leucocyte content (flow cytometry). The Endo-Pat 2000 device (Itamar Medical, Caesarea, Israel) will be used to measure reactive hyperaemia peripheral arterial tonometry as an index of regional endothelial function as previously described^27^ at baseline and at 24 hours post-surgery.

#### Planned recruitment rate

We estimate that we will require 2 years to recruit the target population, assuming the cardiac unit in Glenfield will continue to undertake 1200 adult cardiac cases per year. The recruitment rate will equate roughly to one patient per week. We anticipate an additional 6 months for the completion of follow-up and resolution of database queries. This is based on a similar recruitment strategy to a previous observational study.^26^

#### Measures taken to avoid bias

All necessary steps will be taken to reduce the risk of bias.^28 29^ The trial will be analysed on an intention-to-treat basis, that is, outcomes will be analysed according to the treatment allocation, irrespective of future management and events, and every effort will be made to include all randomised patients. Selection bias will be minimised by concealed randomised allocation. Patients, clinicians and researchers will be blinded to the intervention to minimise procedural bias. Detection bias will be minimised by objective source data verification of the data for the primary endpoint and blinding of laboratory staff analysing biomarkers and inflammatory processes. Detection bias for clinical outcomes that are not part of the primary endpoint will be minimised using objective outcome criteria; as defined in the outcome section above and recorded in a blinded manner. Decisions about discharge from ICU, HDU and from hospital will be made by clinical staff based on existing institutional protocols. ICU/HDU transition will be defined as transition from level 3 (1:1 nursing ratio) to level 2 (1:2 nursing ratio). HDU/ward transition will be defined as time of arrival on the ward. To minimise attrition bias, we aim to include data for all randomised participants in the data analyses.

#### Adverse events

Adverse events will be recorded and reported in accordance with the University of Leicester’s and University Hospitals Leicester NHS Trust’s policies for reporting research-related adverse events. In cardiac surgery, postoperative transient complications are not unexpected and are not infrequent. The research team will only notify deaths and ‘unexpected’ non-fatal serious adverse events (SAEs) to the Trial Sponsor (University of Leicester Research Office). The sponsor will inform the research team which SAEs should be reported to the research ethics committee.

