### Sildenafil as a renoprotective intervention in cardiac surgery

Intravenous sildenafil (Revatio; Pfizer) is a phosphodiesterase (PDE) type 5 inhibitor that acts by inhibiting the breakdown of cGMP, a NO secondary messenger. By upregulating NO activity, it reverses endothelial dysfunction in settings such as diabetes and other inflammatory diseases and has proven clinical efficacy in the management of erectile dysfunction (as Viagra), diabetic cardiomyopathy^19^ and pulmonary hypertension.^20^ Intravenous sildenafil is currently licensed for the treatment of pulmonary hypertension and has orphan designation (EU/3/10/815) for the treatment of postcardiotomy right ventricular failure following cardiac surgery.^21^ In a preliminary dose funding study (REVAKI-1), we demonstrated that sildenafil at a dose of 12.5 mg can be administered safely to patients undergoing cardiac surgery.^22^ This dose achieved plasma concentrations that are clinically effective in humans taking the oral formulation,^23 24^ and similar to the levels observed in the porcine preclinical study, without adverse side effects. Sildenafil administered as a bolus of 10 mg over 10 min followed by an infusion of 2.5 mg over 2 hours did produce a transient drop in blood pressure in some patients; however, this was transient, lasting less than 5 min and was reversible by short-acting vasoconstrictors (phenylephrine, ephedrine) that are routinely used to maintain mean arterial blood pressure within the desired range during anaesthesia. Using this information, we designed a randomised clinical trial to compare this dose with a placebo. The aims of the trial are to compare levels of kidney function and injury in the two groups, as well as markers of injury in other organ systems that may be protected by sildenafil treatment.

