Estimate the difference in serum creatinine levels (measured daily for up to 7 days postoperatively and adjusted for baseline values) between patients allocated to the sildenafil and placebo groups.Estimate the difference in the frequency of AKI (defined as a rise in serum creatinine of >26 µmol/L within 48 hours or a doubling of the serum creatinine within 7 days as defined by the KDIGO criteria)^4^ between patients allocated to the sildenafil and placebo groups. Individuals who receive renal replacement therapy (RRT), including haemofiltration, are considered to have met the criteria for stage 3 AKI irrespective of the stage they are in at the time of RRT.Estimate the difference in biomarkers of postoperative renal injury, and myocardial injury, between patients allocated to the sildenafil and placebo groups.Estimate the difference in the frequency of sepsis, low cardiac output, acute lung, brain or gut injury or death between patients allocated to the sildenafil and placebo groups. These outcomes, along with the primary outcome will also be considered as a composite endpoint.Estimate the difference in Multiple Organ Dysfunction Scores between patients allocated to the sildenafil and placebo groups.Estimate the difference in the frequency of other adverse events not listed above between patients allocated to the sildenafil and placebo groups.Estimate the median difference in hospital length of stay between patients allocated to the sildenafil and placebo groups.Estimate whether sildenafil increases the frequency of adverse drug reactions; specifically hypotension that requires treatment or allergic responses.Estimate whether the observed effects of sildenafil may be attributable to changes in endothelial function.Estimate whether the observed effects of sildenafil may be attributable to changes in platelet, leucocyte or endothelial cell activation.

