### Research procedures

#### Screening and eligibility assessment

The patients’ AKI risk score will be calculated at the preoperative assessment clinic or from our standard in patient referral protocols that include detailed clinical and demographic information (table 2). A patient information sheet (PIS), approved by the local Research Ethics Committee, will be sent by post to all potentially eligible patients waiting at home. For patients waiting in hospital, the PIS will be given to them in person. The patient will have time to read the patient information sheet and to discuss their participation with others outside the research team (eg, relatives or friends) if they wish. Each patient will have at least 24 hours to consider whether to participate or not. In a few cases, this time interval may be less, for example for patients admitted for urgent surgery without prior notification to the waiting list co-ordinator. It is important to include these patients for the applicability of the trial findings since about 50% of patients having cardiac surgery are admitted as urgent cases, and these are often those at greatest risk for AKI. Written informed consent will be obtained prior to surgery. Details of all patients approached for the trial and reason(s) for non-participation (eg, reason for being ineligible or patient refusal) will be documented by the research staff in the form of a screening log that will not contain patient-identifiable information.

**Table 2 T2:** Key data collection points and procedures

	Preoperation	Operation day	Day 1	Day 2	Day 3	Day 4	Day 5	Discharge	6 weeks	3 months
Eligibility	✓									
Written consent	✓									
Concomitant medication concomitant medication only in relation to infection apart from pre op	✓	✓	✓	✓	✓	✓	✓	✓	✓	✓
Pregnancy testing	✓									
Randomisation	✓									
Operative details		✓*								
MODSs	✓	(6–12 hours)	✓ (24 hours)	✓ (48 hours)	✓ (72 hours)	✓ (96 hours)				
Clinical outcomes			✓	✓	✓	✓	✓		✓†	✓‡
Serious adverse event monitoring/adverse events		✓	✓	✓	✓	✓	✓	✓	✓†	✓
Bloods: serum biochemistry (creatinine, amylase, liver function tests) and full blood counts	✓	✓ (CICU* and 6–12 hours)	✓*	✓*	✓*	✓*	✓*§	✓§*	✓	
Organ injury mark*e*rs; urine NGAL, serum troponin	Urine ✓ Troponin I	✓ Troponin I (6–12 hours)	Urine ✓	✓ Troponin I (48 hours)						
RH-PAT testing	✓		✓							
Bloods: citrated whole blood for flow cytometry	✓	✓ (6–12 hours)		✓						
Tracheal aspirate		✓ (4–6 hours)								
Questionnaire									✓	✓

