### Statistical analyses

The primary outcome for the trial will be the serum creatinine values measured postoperatively, adjusted for baseline values. On the basis that observed SD for serum creatinine values from the MARACAS trial was 37 μmol/L, and the mean observed correlation between baseline and six postsurgery measures was 0.84, we estimate that a sample size of 56 patients per group will have a 90% power to detect a mean difference of 10 μmol/L for serum creatinine values over six postintervention time points, between treatment and control groups with an alpha value of 0.05. This equates to a moderate effect size. Additionally, the study has 80% power to detect a 33% reduction in the frequency of AKI, as a secondary endpoint. We propose to recruit 126 patients (63 per group) anticipating that 10% of patients will be treated outside of the protocol, withdrawn or lost to follow-up.

AKI is a key secondary endpoint of interest. If the observed KDIGO AKI event rate was 65%, as observed in the MARACAS trial, a sample size of 59 patients per group will allow us to detect an absolute reduction in the frequency of AKI to 40% with an 80% power and 5% significance (two-tailed).

Specific morbidities and other adverse events are too infrequent for the trial to be able to detect differences between the treatment and control groups. Frequencies of these adverse outcomes will be tabulated, in line with guidelines for reporting adverse events in trials.^29^ Our mechanism substudy will be performed on a subgroup of 96 patients. As this analysis is exploratory, no power calculation was performed.

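### The sponsor-notification rule filters non-fatal SAEs on expectedness alone and makes no exception for events attributed to sildenafil

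*Protocol article*

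**What the plan says.** The Adverse events section opens with a general commitment: "Adverse events will be recorded and reported in accordance with the University of Leicester’s and University Hospitals Leicester NHS Trust’s policies". It then gives a reason for filtering, "In cardiac surgery, postoperative transient complications are not unexpected and are not infrequent", and the filter itself: "The research team will only notify deaths and ‘unexpected’ non-fatal serious adverse events (SAEs) to the Trial Sponsor". Onward reporting depends on the sponsor: "The sponsor will inform the research team which SAEs should be reported to the research ethics committee".

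Two other places bear on the rule. The Introduction, in the section on sildenafil as a renoprotective intervention, describes an earlier dose study that gave a 10 mg bolus and then a 2-hour infusion of 2.5 mg. Of that regimen it reports: "did produce a transient drop in blood pressure in some patients; however, this was transient, lasting less than 5 min". It adds that short-acting vasoconstrictors could reverse the falls. Aims and objectives includes: "Estimate whether sildenafil increases the frequency of adverse drug reactions; specifically hypotension that requires treatment or allergic responses".

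On collection and analysis, Table 2 has a row headed "Serious adverse event monitoring/adverse events", ticked from operation day to 3 months, and Statistical analyses says: "Frequencies of these adverse outcomes will be tabulated, in line with guidelines for reporting adverse events in trials".

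**The concern.** A filter on expectedness makes sense where surgery produces many complications that have nothing to do with the drug. Here, however, the foreseen drug effect overlaps with the surgical background. Hypotension can arise from the operation or from a vasodilator, and the rule does not ask which cause the investigator suspects. The stated rationale concerns surgery only. An event can therefore be expected for a patient after cardiac surgery and at the same time be a suspected reaction to the study drug, and under this rule the first property settles the matter.

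What is at stake is oversight during recruitment. The sponsor chooses what goes to the ethics committee, and under this rule it can choose only among deaths and non-fatal SAEs classed as unexpected. Individual reports also carry more weight than usual here, because Statistical analyses concedes that adverse events will be too rare for a comparison between arms to detect a difference.

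**Working it through.** No figure in the article decides this point, so the check is a reading of the rule against the other sections.

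**Step 1: apply the rule to each type of SAE.**

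| SAE | Judged related to drug? | Classed as expected? | Notified under the rule? |
|---|---|---|---|
| Fatal | either | either | Yes |
| Non-fatal | No | No | Yes |
| Non-fatal | Yes | No | Yes |
| Non-fatal | No | Yes | No |
| Non-fatal | Yes | Yes | No |

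The fourth row is what the stated rationale is meant to exempt. The fifth row is exempted with it, because the rule uses the expectedness column and ignores the relatedness column. The defect is confined to that row.

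**Step 2: could the fifth row contain events?** The article itself supplies a candidate. Falls in blood pressure were seen in the earlier study at 12.5 mg in total (10 + 2.5), the total dose in Table 1. The match is on total dose only: the Introduction describes the earlier bolus as given over 10 min, while Table 1 runs it over 20 min (15 mL at 45 mL/h). Treated hypotension is then named as an adverse drug reaction to be compared between arms. Allergic responses are named too, but they are less easily taken for a routine surgical complication, so hypotension is the stronger example. Only episodes that meet the definition of serious matter here; brief falls of the kind described would usually not.

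**Step 3: look for another described route to the sponsor.**
- Recording: adverse events are recorded under institutional policies and collected to 3 months. The events are captured.
- Tabulation and comparison: frequencies are tabulated and treated hypotension is compared by arm. The Plan of analysis places the primary analysis after follow-up is complete for all patients.
- Local detection: under Measures taken to avoid bias, patients, clinicians and researchers are blinded, so an imbalance by arm would not be apparent to them.
- Central review: Trial management has the trials unit checking data quality as the trial proceeds, and Patient and public involvement mentions research governance committees. The article states no safety remit for either.

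Recording and eventual analysis are therefore secured. Notification of fifth-row events to the sponsor during the trial is not.

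**Step 4: size.** The number exposed is the 63 patients planned for sildenafil, over about 2 years of recruitment. The article gives no rate of serious, non-fatal, drug-attributed events and no list of expected events, so a count of events not notified cannot be derived.

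**The case against.** The best defence is that this is a condensed article. Reporting is said to follow the policies of the university and the hospital trust, which are not shown. Causality assessment, a list of expected events and reference safety information would normally sit there or in the full protocol. That would answer a complaint that something is missing. It does not answer a rule stated in exclusive terms: if the fuller documents do require related SAEs to be notified, the article misstates them, and the sentence still needs correcting.

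A second defence is that nothing in the article classes serious hypotension as expected. The rationale speaks of transient postoperative complications, and the earlier falls were brief and reversible, so a severe or prolonged episode could well be judged unexpected and be notified. This stands. A reader might infer that serious drug-related hypotension would never be notified. The documents support only the conditional statement: it need not be notified if it is classed as expected. Nor can the exemption be assumed to extend to low cardiac output or to myocardial, brain or gut injury, since the article does not call these expected and describes specific morbidities as infrequent.

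A third defence is that events withheld from the sponsor are not thereby hidden. This also stands. A reader might infer that an excess of harm could run unseen to the end of the trial. That would require there to be no other safety review, and an article that mentions governance committees without describing their remit cannot establish this.

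**Conclusion.** The point holds in a limited form. For non-fatal SAEs the rule depends on expectedness alone, its rationale is surgical, and it makes no exception for suspected drug reactions, although the article foresees one and sets out to measure it. The consequence is that a non-fatal SAE attributed to sildenafil need not reach the sponsor if it is classed as an expected surgical complication. This rests on reading the exclusive wording as written and on the unseen policies not overriding it. How often it would happen is unknown. The primary analysis is unaffected. It is a weakness in safety reporting that should be corrected, and it is no evidence that harm would be missed.

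**What to change.** Reconcile the Adverse events section with the adverse drug reaction objective in Aims and objectives. State that the exemption from sponsor notification covers only expected surgical complications judged unrelated to study drug. State also that any non-fatal SAE judged possibly related to study drug is notified to the sponsor, with its expectedness judged against the drug's reference safety information and not against the usual course after cardiac surgery. If the institutional policies already require this, cite the requirement and remove the exclusive wording.

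The cost is a short amendment, a relatedness field on the SAE form, and some additional notifications, whose number cannot be estimated from the article. Unrelated expected complications, for which the filter was written, stay exempt.

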### Statistical analyses

The primary outcome for the trial will be the serum creatinine values measured postoperatively, adjusted for baseline values. On the basis that observed SD for serum creatinine values from the MARACAS trial was 37 μmol/L, and the mean observed correlation between baseline and six postsurgery measures was 0.84, we estimate that a sample size of 56 patients per group will have a 90% power to detect a mean difference of 10 μmol/L for serum creatinine values over six postintervention time points, between treatment and control groups with an alpha value of 0.05. This equates to a moderate effect size. Additionally, the study has 80% power to detect a 33% reduction in the frequency of AKI, as a secondary endpoint. We propose to recruit 126 patients (63 per group) anticipating that 10% of patients will be treated outside of the protocol, withdrawn or lost to follow-up.

AKI is a key secondary endpoint of interest. If the observed KDIGO AKI event rate was 65%, as observed in the MARACAS trial, a sample size of 59 patients per group will allow us to detect an absolute reduction in the frequency of AKI to 40% with an 80% power and 5% significance (two-tailed).

Specific morbidities and other adverse events are too infrequent for the trial to be able to detect differences between the treatment and control groups. Frequencies of these adverse outcomes will be tabulated, in line with guidelines for reporting adverse events in trials.^29^ Our mechanism substudy will be performed on a subgroup of 96 patients. As this analysis is exploratory, no power calculation was performed.

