### Study population and recruitment

The study will be carried out at a single tertiary cardiac surgery centre in the UK. If sildenafil is effective, its clinical benefits and impact on resource use will be most apparent in patients at greatest risk of developing AKI. In the UK, over one-third of patients are at risk of developing AKI.^20 25^ Patients at increased risk of developing AKI will be identified preoperatively using a risk score developed and validated by these investigators in a multicentre population of over 40 000 cardiac surgery patients^1^ that has been designed to enable cohort enrichment for clinical trials on renoprotective interventions in cardiac surgery (http://www.cardiacsurgeryleicester.com/our-research/acute-kidney-injury-risk-score-calculator/).

In the MARACAS study,^26^ using a cut-off of 22% for the score (positive predicted value (PPV 0.55), 1 in 8 patients were eligible, 1 in 15 were recruited and 39/61 patients recruited thus far have developed AKI. The REVAKI-2 trial will use similar eligibility criteria.

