#### Inclusion criteria

Patients may enter the study if ALL of the following apply:

Adult cardiac surgery patients 18 years of age or above undergoing cardiac surgery with cardiopulmonary bypass and cardioplegic arrest.Identified as representing a high-risk group for AKI using a modified AKI risk score; a predicted risk score of 20% equates to a PPV for developing AKI of >55%.Female subjects of childbearing potential are not to be pregnant (to be confirmed by urine human chorionic gonadotropin pregnancy test prior to dosing). Women are considered not to be of childbearing potential if they have been surgically sterilised (eg, tubal ligation, oophorectomy or hysterectomy) or are postmenopausal (defined as serum follicle-stimulating hormone level of ≥30 IU/mL) in the absence of hormone replacement therapy and complete absence of menses for at least 24 consecutive months.Able, in the opinion of the investigator, and willing to give informed consent.

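### The 80% power claimed for a 33% reduction in AKI has no stated scale or control rate, does not reproduce, and conflicts with the 65% to 40% calculation in the next paragraph

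*Protocol article*

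**What the plan says.** All the power statements are in the protocol article, Statistical analyses. The trial is sized on serum creatinine: "we estimate that a sample size of 56 patients per group will have a 90% power". The AKI claim follows directly: "Additionally, the study has 80% power to detect a 33% reduction in the frequency of AKI, as a secondary endpoint". That sentence names no control rate and no scale. The recruitment target comes next (the quotation stops one word short of the end of the sentence): "We propose to recruit 126 patients (63 per group) anticipating that 10% of patients will be treated outside of the protocol, withdrawn or lost to".

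The following paragraph calculates AKI power again. Its premise is "If the observed KDIGO AKI event rate was 65%, as observed in the MARACAS trial", and its result is that "a sample size of 59 patients per group will allow us to detect an absolute reduction in the frequency of AKI to 40" per cent, "with an 80% power and 5% significance (two-tailed").

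Two other places bear on the control rate. Study population and recruitment reports that "39/61 patients recruited thus far have developed AKI", which is 63.9%. Inclusion criteria says that "a predicted risk score of 20% equates to a PPV for developing AKI of >55" per cent.

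**The concern.** The two AKI statements both claim 80% power but describe different effects. A fall from 65% to 40% is 25 points, or 25/65 = 38.5% relative, so it is not a 33% reduction on either scale. If 33% is relative, it is a smaller effect than the one said to need 59 per group, and at the same control rate it cannot also have 80% power at about that size. If 33% means percentage points, it is a much larger effect, and 80% is far too low.

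At stake is how the AKI result will be read. The article calls AKI a key secondary endpoint. A reader who takes the sentence as a relative reduction will judge a non-significant AKI result against a nominal 20% chance of missing a true one-third reduction. The actual chance is about 35–37% with 56 per group and 30–32% with 63 per group.

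**Working it through.** **Inputs.** Control rate 65%, two-sided 5% and 80% power come from the second AKI paragraph. The numbers per group are 56 (the primary calculation), 59 (the AKI calculation) and 63 (randomised; 63 × 0.9 = 56.7 after the 10% allowance). Allocation is 1:1. The scale of the 33% is not stated, so both readings are tested.

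**Formulas.** Let d = p1 − p2, V = p1(1 − p1) + p2(1 − p2), p̄ = (p1 + p2)/2 and V0 = 2p̄(1 − p̄).
- Unpooled: n = (1.960 + 0.842)² V / d²; power = Φ(d/√(V/n) − 1.960).
- Pooled: n = (1.960√V0 + 0.842√V)² / d²; power = Φ((d − 1.960√(V0/n)) / √(V/n)).

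**Step 1: reproduce the plan's own 59 (65% to 40%).** d = 0.25; V = 0.2275 + 0.2400 = 0.4675; p̄ = 0.525; V0 = 0.49875.
- Unpooled: n = 7.849 × 0.4675 / 0.0625 = 58.7, rounded up to 59. The stated figure reproduces.
- Pooled: n = 61.4, rounded up to 62.

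**Step 2: 33% as a relative reduction.** p2 = 0.65 × 0.67 = 0.4355; d = 0.2145; V = 0.2275 + 0.2458 = 0.4733; p̄ = 0.54275; V0 = 0.4963.
- n for 80% power: unpooled 7.849 × 0.4733 / 0.04601 = 80.7, so 81; pooled 83.5, so 84.
- Power at 56, unpooled: √(0.4733/56) = 0.0919; 0.2145/0.0919 − 1.960 = 0.373; Φ = 64.5%.
- Power at 56, pooled: √(0.4963/56) = 0.0942; (0.2145 − 1.960 × 0.0942)/0.0919 = 0.326; Φ = 62.8%.

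**Step 3: 33% as an absolute reduction.** p2 = 0.32; d = 0.33; V = 0.4451; V0 = 0.4996. n for 80% power is 32.1 (unpooled) or 34.8 (pooled), so 33–35 per group.

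**Results (power, pooled / unpooled):**

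| Scenario | 56 per group | 59 per group | 63 per group | n for 80% |
|---|---|---|---|---|
| 65% to 43.6% (33% relative) | 62.8 / 64.5% | 65.1 / 66.8% | 68.0 / 69.7% | 84 / 81 |
| 65% to 40% (the plan's second claim) | 76.2 / 78.1% | 78.4 / 80.2% | 81.0 / 82.7% | 62 / 59 |
| 65% to 32% (33 points) | 94.8 / 95.9% | 95.8 / 96.7% | 96.8 / 97.5% | 35 / 33 |

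**Step 4: can another reading rescue the 80%?**
- Exact enumeration of the uncorrected chi-square test for the relative reading gives 62.0% at 56 and 70.5% at 63.
- Taking one-third instead of 33% gives 63.7% at 56 and 68.9% at 63 (pooled).
- Using the observed 39/61 as the control rate gives 61.2% at 56 (pooled).
- A one-sided 5% test with all 63 per group gives 78.5%, but the plan states a two-tailed test.
- Two-sided 80% power for a 33% relative reduction would need a control rate of about 73% (63 per group) to 76% (56 per group). The article gives no such rate.

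**The case against.** The strongest reply is that the correct scenario already stands in the next paragraph, that only a secondary endpoint is involved, and that results will be reported with 95% confidence intervals, so a null AKI result need not be read through pre-trial power. That limits the importance of the point but does not make the sentence right.

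Three stronger inferences are tempting, and the document does not support them.

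- *That power for a 33% relative reduction is simply 63%, because only 56 per group will be analysed.* The 10% allowance includes patients treated off protocol. The primary analysis is by intention to treat, and Measures taken to avoid bias aims to include all randomised participants, so these patients stay in. AKI is determined within 7 days, largely from routine creatinine samples. The analysed number therefore lies between 56 and 63, and the range must be shown. Even at 63, power is only 68–70%.
- *That the 59-per-group figure is also wrong.* It reproduces with a standard unpooled formula and is below the 63 randomised. With all 63 analysed, 65% versus 40% has 81–83% power. Only if the number falls to 56 does it drop to 76–78%.
- *That the control rate should be 55%.* The article gives this as a lower bound (above 55%) for the risk score, while 39/61 supports the 65% used. At 55%, power for a 33% relative reduction would be about 49–50% at 56 per group, but showing this is optional.

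It is also fair that the sentence never says relative. Under the absolute reading, 80% understates the power. That is why the defect is an undefined and inconsistent claim, and not simply an overstated one.

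**Conclusion.** The point holds for the 33% sentence alone. It is undefined, no two-sided reading at a documented control rate gives 80%, and it contradicts the paragraph after it. On the relative reading, power is about 63–70% across 56–63 per group, and 80% needs about 81–84 per group. On the absolute reading, it is about 95% or more. These figures assume a 65% control rate, a two-sided 5% test, 1:1 allocation and an unadjusted comparison of two proportions without continuity correction.

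A reader might infer that the trial is too small and must be enlarged. The document does not support that: the size is set by serum creatinine, and the key secondary endpoint already has a supportable calculation in 65% versus 40%.

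**What to change.** Delete the 33% sentence, or restate it with its scale, control rate and analysed number. Keep one AKI power statement, for example: with a 65% control rate and a two-sided 5% test, 65% versus 40% has about 76–78% power if 56 per group are analysed and about 81–83% if all 63 randomised per group are analysed by intention to treat; a 33% relative reduction has about 63–70% power across that range. Figures for a 55% control rate may be added but are not required.

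The 59-per-group calculation can stay; naming its formula (unpooled variance) would let a reader reproduce it. Keep the sample size. The cost is wording only: endpoint, analysis and recruitment do not change, and the stated power for a one-third relative reduction becomes less favourable.
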